## Abstract

**Background:**

The rational use of antibiotics is of great importance in health care. In primary care, acute respiratory infections are the most common cause of inappropriate antibiotic prescribing. Since existing studies aiming to optimize antibiotic use are usually based on the voluntary participation of physicians, general practitioners (GPs) with inappropriate prescribing behavior are underrepresented. For the first time in Germany, the ElektRA study will assess and compare the effects of three interventions on antibiotic prescribing rates for respiratory and urinary tract infections among high prescribers in primary care.

**Method:**

ElektRA is a 4-arm cluster-randomized controlled trial among German GPs in nine regional Associations of Statutory Health Insurance Physicians. On their behalf, the Central Research Institute of Ambulatory Health Care in Germany (Zi) analyses all outpatient claims and prescription data. Based on this database, high antibiotic prescribing GPs are identified and randomized into four groups: a control group (*N*=2000) and three intervention arms. We test social norm feedback on antibiotic prescribing (*N*=2000), social norm feedback plus online training on rational prescribing practice and communication strategies (*N*=2000), and social norm feedback plus online peer-moderated training on rational antibiotic prescribing, communication strategies, and sustainable behavior change (*N*=1250). The primary outcome is the overall rate of antibiotic prescriptions. Outcomes are measured before intervention (T0, October 2020–September 2022) and over a period of 15 months (T1, October 2022 to December 2023) after randomization.

**Discussion:**

The aim of the study is to implement individualized, low-threshold interventions to reduce antibiotic prescribing among high prescribers in primary care. If successful, a change in behavior among otherwise difficult-to-reach high prescribers will directly improve patient care. The increase in quality of care will ideally be achieved both in terms of the quantity of antibiotics used as well as the kind of substances prescribed. Also, if effective strategies for high prescribers are identified through this study, they can be applied not only to the antibiotics addressed in this study, but also to other areas of prescription management.

**Trial registration:**

Current Controlled Trials ISRCTN95468513.

**Supplementary Information:**

The online version contains supplementary material available at 10.1186/s13012-022-01241-4.

Contributions to the literature
Previous studies on reducing antibiotic prescribing in primary care are based on voluntary participation. Physicians with high prescribing behavior are underrepresented.ElektRA specifically targets “high prescribers” who often lack sensitivity to the issue and perceive their own prescribing behavior as unproblematic.To our knowledge, no study has yet attempted to identify and optimize high antibiotic prescriptions in primary care in Germany.We test usual care in comparison to three interventions that include social norm feedback on antibiotic prescribing, communication strategies, and sustainable behavior change through letters, online training, and peer-moderated online training.

## Background

Antibiotics are an essential part of therapy for severe bacterial infections. However, their effectiveness is threatened by increasing levels of antibiotic resistance [1]. Therefore, before prescribing antibiotics, the benefits of antibiotic use should be weighed against possible harm, both from a micro and a macro perspective. Inappropriate antibiotic use as well as the non-rational prescription of broad-spectrum and/or reserve substances should be avoided.

In Germany—as in many other Western countries—80–90% of antibiotics are prescribed in primary care [2]. Thereby, acute respiratory tract infections (ARTI) are the most frequent cause of the prescription of antibiotics. However, in many of these cases, antibiotic use is unnecessary or inappropriate. While most physicians have a moderate prescription rate, there is a group of physicians who, compared to their colleagues, disproportionately prescribe antibiotics in general or certain groups of active agents. In 2015, almost one third of German general practitioners (GPs) belonged to the group of so-called high prescribers [2]. In the last years, various studies and initiatives have addressed the issue of rational antibiotic use and attempted to influence prescription rates at the regional and national levels through awareness-raising, knowledge transfer, and training [3–6]. However, all these studies were based on voluntary participation. Consequently, high prescribing physicians are underrepresented, and the studies are therefore prone to selection bias. According to current knowledge, the main reasons for the lack of participation of physicians with high prescription rates of antibiotics in studies are their lack of sensitivity to the topic and the perception that their own prescribing behavior is unproblematic [2]. International evidence shows that high prescribers can be motivated to change their prescribing behavior through targeted approaches [7–10]. However, the measures used differ in their approach and effectiveness and are partly dependent on the functioning and organization of the respective health system. To our knowledge, no study has sought to identify and optimize high antibiotic prescribing in primary care in Germany.

### Objectives

The aim of the ElektRA (“Elektive Förderung Rationaler Antibiotikatherapie”—Elective Promotion of Rational Antibiotic Therapy) study is to identify which of the interventions tested in other countries is transferable to the German health care setting and best at gaining access to the group of high prescribers of antibiotics and at sustainably reducing the antibiotic prescription rate for typical treatment occasions such as acute infections. Because of their importance in primary care, we focus on respiratory and urinary tract infections [11]. In addition, the aim is to promote the quality of prescribing with regard to the choice of an active agent. The primary outcome of the study is the overall rate of antibiotic prescriptions, measured as the proportion of patients with antibiotic prescriptions out of all patients with a prescription. Secondary outcomes are the overall prescription rates before and after the intervention for cephalosporins and fluoroquinolones separately. Also, to be explored is whether there are differences in the level of the effects achieved among groups. Factors explored will include region, patients’ multimorbidity, indications of the respective active agent, and failure of previous therapy. A mixed methods evaluation is also carried out.

## Methods

### Trial design

The ElektRA study is a 4-arm cluster-randomized controlled trial addressing high antibiotic prescribers among German GPs of nine regional Associations of Statutory Health Insurance Physicians (ASHIP). On their behalf, the Central Research Institute of Ambulatory Health Care in Germany (Zi) analyses all outpatient claims and prescription data (T0, October 2020–September 2022). Based on this data set, we can identify GPs who use antibiotics or problematic agents (e.g., fluoroquinolones) more frequently than their colleagues. From this pool, GPs are randomized into four groups: a non-contacted control group and three intervention arms (A–C). Within these arms, we test (A) *social norm feedback* on antibiotic prescribing, (B) *social norm feedback* plus *online training* on rational prescribing practice and communication strategies, and (C) *social norm feedback* plus *online peer-moderated training* on rational antibiotic prescribing, communication strategies, and sustainable behavior change. Randomization is stratified by region. GPs in groups A–C will be contacted by their respective regional ASHIP. The primary outcome is the overall rate of antibiotic prescriptions, measured as the proportion of patients with antibiotic prescriptions out of all patients with a prescription. Outcomes are measured over a period of 15 months (T1, October 2022–December 2023) after randomization. In addition, a mixed-method process evaluation is carried out.

### Data basis

The data basis is the pseudonymized German prescription data (according to § 300 SGB V) and outpatient claims data (according to § 295 SGB V). Since the processing of these data takes place within the framework of tasks of the regional ASHIP defined in the German Social Security Code SGB V, processing of the data is possible without a declaration of consent. Despite the fact that an ethics vote is not mandatory for secondary data analyses [12], it was obtained for the evaluation study in general from the Ethics Committee of the Rostock University Medical Center. Since no informed consent must be obtained before randomization, ElektRA has a real control group that is not aware of the study and the interventions. Distortions due to the Hawthorne effect are thus excluded. A selection bias can also be ruled out among the intervention participants, since not only GPs who are motivated and interested receive an intervention. For the evaluation, a total of at least 13 quarters are analyzed. To ensure that the prescribing behavior before the intervention can be examined sufficiently and independently of seasonal fluctuations, at least 8 quarters are used to determine the baseline. For the follow-up data from 5 quarters are available.

### Participants

The Zi uses a summative score to determine potentially eligible GPs and GP practices based on German prescription and outpatient claims data before intervention (T0, October 2020–September 2022). The maximum score value is six. A GP or GP practice obtains one additional point if its own value in one of the aspects exceeds the 75% percentile of antibiotic prescribing within the respective region. Here, a region represents the area for which a participating ASHIP is responsible. In Germany, there are in total of 17 of those regions, 9 of which are participating in this study. For inclusion, more than two points are necessary. The aspects listed in Table 1 are used for score formation.

**Table 1 Tab1:** Aspects considered for score formation

1	Overall prescription rate (ratio of patients with antibiotic prescriptions to patients with any prescription)
2	Prescription rate for upper respiratory tract infections (ratio of patients with upper respiratory tract infection to antibiotic prescriptions for these patients)
3	Prescription rate for lower respiratory tract infections (ratio of patients with lower respiratory tract infection to antibiotic prescriptions for these patients)
4	Prescription rate of fluoroquinolones (2 points possible): total prescription rate of fluoroquinolones (ratio of patients with fluoroquinolone to patients with antibiotic) and/or fluoroquinolone prescription rate for urinary tract infection (ratio of urinary tract infection patients with fluoroquinolone to urinary tract infection patients with antibiotics)
5	Prescription rate of cephalosporins (ratio of patients with cephalosporin to patients with antibiotics)

After identification, the GPs or GP practices meeting the inclusion criteria are randomized and stratified by region. As identification is based on pseudonymized data, an independent trust center will generate study pseudonyms that will enable all participating regional ASHIP and the Zi to communicate about identified entities and allow the ASHIP to re-identify these eligible GPs or GP practices and contact them. The Zi on the other hand will always exclusively work with pseudonymized data to compile all further analyses, e.g., those necessary for providing GP-specific prescription feedback. Physicians who have already participated in the RESIST Innovation Fund project [13] are excluded because they have already received e-learning on optimizing antibiotic prescribing.

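### Table 1 prints the upper and lower respiratory prescribing items as reciprocals of a prescribing rate, so two of the six eligibility points, read literally, reward low respiratory prescribing

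*Protocol article*

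**What the plan says.** The section Participants sets out the eligibility score. A GP or practice "obtains one additional point if its own value in one of the aspects exceeds the 75% percentile of antibiotic prescribing within the respective region". On the total: "The maximum score value is six". On the threshold: "For inclusion, more than two points are necessary".

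Table 1 lists the aspects scored:

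- Item 1, the overall rate, is the "ratio of patients with antibiotic prescriptions to patients with any prescription". The antibiotic count comes first.
- Item 2 is "Prescription rate for upper respiratory tract infections (ratio of patients with upper respiratory tract infection to antibiotic prescriptions for these patients".
- Item 3 is "Prescription rate for lower respiratory tract infections (ratio of patients with lower respiratory tract infection to antibiotic prescriptions for these patients".
- Items 4 and 5 put the fluoroquinolone or cephalosporin patients first and the antibiotic-treated patients second.

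The section Trial design gives the purpose: to pick out GPs who use antibiotics or problematic agents more often than their colleagues. No other section restates or corrects items 2 and 3.

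**The concern.** In items 1, 4 and 5 a ratio of X to Y means X divided by Y, and a high value means heavy prescribing. If the same convention holds for items 2 and 3, infection patients are divided by antibiotic prescriptions. That is the reciprocal of prescriptions per infected patient. The point is still awarded for a high value, so it would go to practices that prescribe least for respiratory infections.

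Table 1 is the only definition given of the rule that decides who is eligible for randomisation and so who may receive the feedback letter. Respiratory infections are one of the two infection groups on which the article focuses. If the printed ratio were computed, some heavy respiratory prescribers would be left out and some restrained ones let in. The trial population would then no longer be the high prescribers it is described as. The control rate of 12% in the section Sample size is taken from high prescribers in a predecessor project, so that assumption would also be less secure.

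**Working it through.** **1. Reproduce the stated maximum.** Items 1, 2, 3 and 5 carry one point each and item 4 carries two: 1 + 1 + 1 + 2 + 1 = 6. This agrees with the article. More than two points means at least 3 of 6.

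**2. Direction of items 2 and 3.** Let n be the infection patients and r the antibiotic prescriptions for them. As printed, the value is n/r = 1/(r/n), which falls strictly as prescribing per patient, r/n, rises. Exceeding the 75th percentile of n/r is therefore the same as lying in the bottom quarter of r/n.

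Illustration with assumed counts, five practices with 200 infection patients each:

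| Antibiotic prescriptions | As printed (n/r) | Turned round (r/n) |
|---|---|---|
| 20 | 10 | 0.10 |
| 40 | 5 | 0.20 |
| 60 | 3.33 | 0.30 |
| 80 | 2.5 | 0.40 |
| 120 | 1.67 | 0.60 |

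The 75th percentile of the five values is 5 as printed and 0.40 when turned round. The point goes to the practice with 20 prescriptions in the first case and to the one with 120 in the second. The example shows direction only; real cut-offs depend on regional distributions that the article does not give.

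**3. What two reversed items can do to the total.** They give at most 2 points against 3 needed, so at least one point must come from high overall, fluoroquinolone or cephalosporin prescribing. A practice with one such point that is in the lowest quarter on both respiratory items would score 1 + 2 = 3 and enter. A practice with one such point that is in the highest quarter on both would score 1 + 0 = 1 and be left out.

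**4. How many practices change status.** The article gives no correlation between items, so this step is an assumption shown over a range. 20,000 practices were simulated with six equally correlated normal scores, a point above the 75th percentile, and inclusion at 3 or more points. Items 2 and 3 were scored in the intended and in the printed direction.

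| Assumed correlation | Included, intended direction | Included, as printed | Intended practices kept | Printed-rule practices that also qualify as intended |
|---|---|---|---|---|
| 0 | 17% | 17% | 46% | 46% |
| 0.4 | 24% | 17% | 55% | 78% |
| 0.7 | 26% | 18% | 68% | 96% |

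The first row can be checked by hand. With independent items, the chance of at least 3 of 6 points at 0.25 each is 1 − (0.1780 + 0.3560 + 0.2966) = 0.1694. A practice qualifies under both directions in two ways:

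- It has 3 or 4 points from the four unaffected points: 0.0469 + 0.0039 = 0.0508.
- It has exactly 2 of those (0.2109) and is high on one respiratory item and low on the other (2 × 0.25 × 0.25 = 0.125): 0.2109 × 0.125 = 0.0264.

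The sum is 0.0772, and 0.0772/0.1694 = 0.46, which agrees with the simulation.

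**The case against.** The strongest reply is that the context leaves only one sensible reading. Both items are labelled as prescription rates. The percentile rule refers to antibiotic prescribing, not to an unlabelled ratio. The other items run in the usual direction, and the aim is to find heavy prescribers. On this view the parentheses contain a slip and the score was programmed correctly. This stands as the likely explanation. It does not remove the contradiction: the only printed definition is the reverse of what is meant, and the article does not show the implementation.

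A reader might infer more than the documents support:

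- **That the sponsor chose this direction or has applied it.** The label and the aim argue against a deliberate choice, and nothing shows what was computed. The article mentions SQL code only for assigning random numbers.
- **That restrained prescribers could enter on respiratory items alone.** They could not, because 2 points fall short of 3.
- **That the comparison between arms would be biased.** Eligibility is settled before allocation and applies alike to all four groups.
- **That restrained GPs would be told they are high prescribers.** The section Interventions describes a letter that sets each GP's own figures against those of regional peers, so they would see their own values.

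Items 2 and 3 also count prescriptions where the other items count patients. Prescriptions per infected patient is a workable measure, so this is an inconsistency for which no harm has been shown.

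**Conclusion.** The concern holds as a contradiction within the operative eligibility rule. Items 2 and 3 as printed are reciprocals of the rate they are named for. Followed literally, up to 2 of 6 points would reward the lowest respiratory prescribing. The direction is certain, since it follows from algebra.

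The practical consequence depends on whether the printed ratio is the one computed, which the documents leave open. If it were, the damage would be to who is studied: some high prescribers excluded, others wrongly admitted, and the target population diluted. Randomised comparisons would remain internally valid. The loss of roughly a third to a half of correctly qualifying practices (68% to 46% kept) rests on assumed equal correlations from 0.7 down to 0 and is illustrative.

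**What to change.** Restate items 2 and 3 with antibiotic treatment in the numerator and infection patients in the denominator. The preferable form is patients with an upper (or lower) respiratory infection who received an antibiotic, divided by all patients with that infection. This matches the patient-based items and settles that a patient with repeat prescriptions counts once. If prescriptions per infection patient is what was meant, say so and keep that numerator.

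Confirm before randomisation that the implemented score uses the stated definition and direction. If allocation has already taken place, report which direction was used.

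The cost is two table rows and one check of the score code. If the code already runs the right way, nothing else changes; if not, the eligibility list has to be regenerated before allocation.

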### Recruitment

Nine regional ASHIPs participate in the trial (Baden-Württemberg, Bavaria, Bremen, Hesse, Lower Saxony, North Rhine, Saarland, Schleswig-Holstein, Westphalia-Lippe). Based on the procedure described above, eligible GPs will be contacted by their respective regional ASHIP with a letter containing social norm feedback and in case of intervention groups B and C an invitation to participate in an online training or an online peer-moderated training.

### Randomization

Randomization into four groups (control group and three intervention arms A-C) will be stratified by regional ASHIP and will be carried out by the Zi that is not involved in study conduct and implementation. For randomization, the sql-code, which assigns a random number to all included GPs, is used. The individual GP-random number combinations, ranging from *n*_*i*_ to *m* (number of all GPs that need to be included), are sorted according to the following scheme: If the random number is between 1 and *n*_1_, the corresponding GP is assigned to Group A (*n*_1_= defined number of GPs in that group), if it is between *n*_1_+1 and *n*_2_, the GP is assigned to Group B. The procedure for group C and the control group is analogous, whereas *m*-*n*_i_ describes the size of the control group. GP-random number combinations greater than *m* are not assigned to any group.

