### Sample size

We assume that a total antibiotic prescription rate of 12% (rate of high prescribers in the predecessor project RESIST, unpublished data) will be observed in the control group. This rate is expected to be reduced to 8.7% in group A, to 8% in group B, and to 7% in group C. Since all interventions shall be compared to the control, we adjust for multiple testing via the Bonferroni correction and hence the type 1 error is set to 1.67% (two-sided). A Poisson model was used for sample size calculation. To be able to show the effect assumed for the comparison between the control group and group A with a power of 80%, 2000 practices are required in both groups. Due to the feasibility, maximal 1250 practices can be included in group C for comparison to the control. Thereby a power of 98.8% can be gained. Group B consists of 2000 practices to include all remaining eligible practices in all nine participating regional ASHIP. For the comparison between the control group and group B, a power of 94.6% can be gained. This sample size calculation refers to the intention-to-treat (ITT) population. This population includes all randomized practices regardless of whether they accept the offer of training in groups B and C. However, we are also interested in the per-protocol (PP) population which is analyzed within a secondary analysis. The PP population includes only those practices in groups B and C that participated in the training courses according to protocol. Thus, only the assumed effects between the control group and groups B and C change. We assume that in group B, the rate in this population can be reduced to 7.5%. Furthermore, we assume a participation rate between 30% and 40%, i.e., between 580 and 800 practices participate in the online training. Assuming this difference and the Bonferroni adjusted type 1 error of 1.67 a power between 80% and 89% can be gained. In group C, we assume a participation rate between 17% and 20%, i.e., between 215 and 250 physicians will presumably participate in the peer-moderated online training. Under the assumption of a reduction to 6% and the Bonferroni adjusted type 1 error of 1.67 a power between 80% and 85.8% can be gained See Fig. 2.

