**Fig. 2 Fig2:**
[figure not shown]
CONSORT flow diagram, estimations on eligibility are based on data of 2020, T0 data from October 2020 to September 2022 is analyzed retrospectively. Source: http://www.consort-statement.org/, Version of 2010 (12.11.2021)

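### The allocation rule and the sample-size section disagree on what happens if the eligible pool is not 7250, and a surplus would go unused although it could serve as extra controls at almost no cost

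*Protocol article*

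**What the plan says.** The Randomization section of the protocol article prints the allocation rule. It starts with the lowest numbers: "If the random number is between 1 and *n*_1_, the corresponding GP is assigned to Group A". The next block, up to a second cut-point, goes to B. C and then control are filled in the same way, and control is what is left over: "whereas *m*-*n*_i_ describes the size of the control group". The bound m is the "number of all GPs that need to be included". For a pool larger than that, "GP-random number combinations greater than *m* are not assigned to any group".

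The Abstract plans 2000 units each for control, A and B, and 1250 for C. The Sample size section gives the reasons: control and A need 2000 each for 80% power, C is limited by feasibility, and "Group B consists of 2000 practices to include all remaining eligible practices in all nine participating regional ASHIP".

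The legend of Fig. 2 adds that "estimations on eligibility are based on data of 2020". The Participants section takes actual eligibility from a score on data of October 2020 to September 2022, and excludes physicians who took part in RESIST.

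**The concern.** Two sections name different arms as the one that absorbs the rest of the pool. Under Randomization it is control, up to m, and anything beyond m is left out. Under Sample size it is B, which is meant to use up the eligible practices. If the count is exactly 7250, both hold. If it is not, they cannot both govern, and the count was estimated from an earlier period than the one used for inclusion.

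The choice matters because control is the comparator in all three confirmatory tests, and A versus control is planned with only 80% power. Control is also the arm that is cheapest to enlarge. Control GPs are not contacted (Control group), no consent is needed (Data basis), and outcomes come from routine claims and prescription data (Data collection, completeness, and quality). An eligible GP who is left unassigned at random is already in the control condition.

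**Working it through.** **Inputs from the protocol article.** Arm sizes: 2000 (control), 2000 (A), 2000 (B), 1250 (C). Rates: 12% in control, 8.7% in A, 8% in B, 7% in C. Two-sided alpha is 0.05/3 = 1.67% per comparison, with a Poisson model (Sample size).

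**Pool implied by the plan.** m = 2000 + 2000 + 1250 + 2000 = 7250, in the ratio 8:8:5:8 (29 parts of 250).

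**Reproducing the stated power.** With one unit of exposure per practice,

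power = Φ( |r0 − r1| / √(r0/n0 + r1/n1) − z ), with z = 2.394.

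For A: 0.033 / √(0.12/2000 + 0.087/2000) = 0.033 / 0.010173 = 3.244, and Φ(3.244 − 2.394) = 80.2%. The same formula gives 94.6% for B and 98.8% for C. The stated figures are 80%, 94.6% and 98.8%, so the protocol's own model can be used for what follows.

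**Applying the rule.** The cut-points are 2000, 4000, 5250 and 7250. The documents give no shortfall or surplus, so the percentages below are assumptions.

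- Pool 10% over (7975): A, B, C and control reach their planned sizes, and 725 units are unassigned.
- Pool 10% short (6525), cut-points fixed: A 2000, B 2000, C 1250, control 1275.
- Pool of 5000, cut-points fixed: A 2000, B 2000, C 1000, control 0. Control alone takes the loss only up to 2000 units, which is 2000/7250 = 27.6%. Beyond that C loses too.

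**Surplus: power for A versus control**

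| Assumed surplus | Left unassigned | Sent to control |
|---|---|---|
| 5% | 80.2% | 84.2% (control 2362) |
| 10% | 80.2% | 87.1% (control 2725) |
| 20% | 80.2% | 90.9% (control 3450) |

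With variance taken as proportional to 1/n, a control arm of 2725 gives (1/2725 + 1/2000) / (1/2000 + 1/2000) = 0.867 for A and B, a fall of about 13%. For C (n = 1250) the ratio is 0.898, a fall of about 10%. With the Poisson variance the figure for A is (0.12/2725 + 0.087/2000) / (0.207/2000) = 0.846, a fall of about 15%.

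**Shortfall: power for A versus control, cut-points kept fixed**

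| Assumed shortfall | All on control | Shared in proportion |
|---|---|---|
| 5% | 74.5% (control 1638) | 77.9% |
| 10% | 66.2% (control 1275) | 75.3% |
| 15% | 54.0% (control 912) | 72.5% |
| 20% | 36.2% (control 550) | 69.4% |

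At 10%, power for B is 85.5% against 91.9% if shared, and for C 95.4% against 97.8%.

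**If B were the residual arm**, as the Sample size section can be read, a 10% shortfall would leave B with 1275. A versus control would stay at 80.2% and B versus control would be 88.8%. The two sections therefore lead to different trials.

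**The case against.** The strongest reply is that no shortfall is documented and the text does not say that the cut-points are frozen. The Participants section places randomization after identification, when the pool is known, so regional cut-points may be set then. Regional numbers are a detail that an article may leave to the full protocol. Eligibility is also relative to each region's 75% percentile, so a general fall in prescribing would not by itself shrink the pool. Fig. 2, which is not shown, may give an eligible number with a reserve. All of this stands, and it makes the shortfall half conditional. Fixed sizes remain the natural reading of a defined number per group, and lowering m alone would not help, because control is what is left after A, B and C.

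A second reply is that the Sample size sentence only explains why B was set at 2000 and is not an allocation rule. That is possible. The article then still has one section that uses up the estimated pool and another that provides for units beyond it.

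A reader might infer that leaving a surplus unassigned is a flaw in validity. It is not: the omitted units are chosen at random, so no bias arises, and the planned sizes and power are kept. A reader might also infer that every shortfall falls wholly on control. This holds only up to 2000 units, or up to the regional control quota if quotas are regional.

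**Conclusion.** The point holds as a modest but concrete one. The Randomization and Sample size sections do not agree on which arm absorbs a deviation from the estimated pool, and the printed rule forgoes precision that would cost almost nothing to keep. With a 10% surplus sent to control, A-versus-control power would be about 87% instead of 80%. If the cut-points stay fixed and the pool is 10% short, it would be about 66%, against about 75% with the loss shared.

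This rests on four assumptions: the size of the surplus or shortfall; fixed cut-points, for the shortfall half; m = 7250 in the units randomized (Randomization counts GPs, Sample size counts practices); and the protocol's own Poisson model at the Bonferroni level. The planned Dunnett procedure is less conservative, so absolute power would differ somewhat. With exactly 7250 eligible, nothing changes.

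**What to change.** Before allocation, state one rule and set the regional cut-points from the actual T0 pool:

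- If the pool is 7250 or smaller, split it 8:8:5:8 within each region, with C capped at 1250 overall.
- If it is larger, fill A, B and C to their planned sizes and assign every remaining eligible unit to control. The 8:8:5:8 ratio does not apply in this case.
- Keep the fixed effect for regional ASHIP in the model, which allows for control-to-intervention ratios that differ between regions.
- Replace the sentence that leaves units unassigned, and reword the reason for B's size in the Sample size section to match.

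The cost is a few lines of allocation code and protocol text. No letters, contacts or data collection are added. The downside is that the control size is known only after scoring, and that control-to-intervention ratios may vary by region.
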